**13.01.17**

## **Aims**

We aim to develop risk prediction tools that can be used by retinopathy screening services to define the optimal interval to next screening in the national screening programme taking into consideration past screening records and other covariates available in SCI-DM

## **Objectives**

To further this aim we will

- 1) first calculate the currently observed age and sex and diabetes type specific rates of first referable retinopathy in the screening programme and describe these by calendar year
- 2) Build a predictive model and validate its prediction performance of time to first referable disease
- 3) Extend that model to utilise a hidden markov model derived measure of risk and assess whether this improves predictive performance
- 4) compare the estimated number of screenings required to maintain interval disease rate below a given threshold using the maximally predictive model from this process with a much simpler decision algorithm such as the current programme and a programme that would screen all type 1s annually and all types 2s biannually.

The models will be developed for type 1 and type 2 separately

## **Data sources**

Scotland:

Anonymised data from a national clinical database of all patients with a READ code in their clinical record for diabetes mellitus (The Scottish Care Information – Diabetes Collaboration -SCI-DC/SCI-DM) system or more recently SCI-Diabetes). The assignment of such a diagnostic code triggers entry to the database. The most recently available data is the SCI-DM extract of May 2014 but this is currently being updated with data to late 2016.

SCI-DC data contain extensive info including all clinical measurements lab tests urine tests and issued prescriptions as well as annual retinopathy screening data. The data are linked anonymously to hospital admissions data (Scottish Morbidity Record SMR-01), held by the Information Services Division of the National Health Service (NHS) back to 1981, and death data held by the General Register Office for Scotland, using the CHI healthcare number with probabilistic linkage (mal-linkage rate <3%) [1].

## **Inclusion criteria, entry and exit times**

The study will focus on the diabetes population aged 12 years and upwards since this is the group eligible for screening in national policy.

*Type 1 diabetes* : is defined by an algorithm that starts with the clinical assignment of type 1 in the clinical record but then excludes anyone with evidence of type 2 based on extensive oral prescription drug use or more than a year from diagnosis to insulin.

Type 2 diabetes: is defined by the clinical assignment of type 2 unless there is evidence to contradict this.

*Date of diagnosis*: this is taken from SCI-DM – in a small % of cases date of diagnosis is not known and earliest date known to have diabetes has to be used instead.

*Study start date*: 01/01/2007

*Study end date*: 01/06/2016

*Patient entry date* is defined as the latest of study start date, the date of diabetes diagnosis, and the date first evaluable for events (as defined below). Note that for the modelling purposes patient entry date will be further refined to be S2 day +1.

*Patient exit date* for a patient is the earliest of

- i) study end date,
- ii) the date of death,
- iii) the date last evaluable for events (as defined below)
- iv) or the date of the first event of interest.

Those who exit before an event or study end date are considered to be censored.

*Date first evaluable for events*

The dates from which individual patients are first considered evaluable for events are estimated from the dates of when either clinical measures (BMI, HbA1C and blood pressure [BP]) or drug prescription data are first available for that person, since these records confirm that a patient was in Scotland at the time and can therefore be considered evaluable for events.

*Date last evaluable for events*

The date last observable for events is defined as the earliest of

- i) the date last observable for routine data or drug data (i.e. exit from the country) whilst not under admission to hospital plus an additional 183 days
- ii) death, or 01/06/2016; Sensitivity analyses will evaluate the impact of this 183 day period which is in place so as not to censor people too early who simply haven't had any contact with clinical services during the period but who are still under observation.
- iii) *Date of suspension from screening for non eye disease related reason. Such patients can re-enter once the suspension has been lifted as evidenced by a further screening event*

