### *Data formatting*

The data are split longitudinally from a patient's entry date to their exit or censor date using time-intervals defined by screening episodes. If a patient has had 5 screening episodes after entry (so s1 s2 then 5 after that) this would mean that they have 5 rows in the dataset. Covariates get updated at each screening episode.

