### *Event dates*

The date of the event will be taken as the date of screening on which referable retinopathy was detected. Each person time interval has a binary flag for whether an event occurred in a person-time interval.

We also have a censor date (which is the earliest of death/event/study end date/end of observability). If a person is censored and his event flag is 1, then that means he was censored because of the event. If at the person's last time-interval the event flag is 0, then he was censored for one of the other reasons (i.e. akin to a SURV object in R for Cox regression).

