### **Initial tabulations**

For each continuous covariate being considered :

- Summarise its distribution as mean median sd iqr and range and plot its distribution (density or histogram) plot
- Tabulate the frequency of all categorical variables

Events:

- Show the number (%) and event rate of incident events during follow up By AGE and SEX and diabetes type
- By Sex strata and for broad age bands and all ages combined show the age standardised event rate for each of the event of interest standardised to the 2013 European Standard Population

Then with any referable retinopathy as the event of interest :

- Summarise the distribution of follow up time range of person entry and exit dates
- Summarise the distribution of covariates at baseline by subsequent event status

- In the same table show the p value and the beta regression coefficient for the current age - sex -and diabetes duration -adjusted associations of all variables with the outcome

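### The S2 day +1 entry is limited to modelling, so the Objective 1 and tabulated event rates count referable disease already present at a first screening as incident

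*SAP*

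**What the plan says.** In the SAP, Inclusion criteria, entry and exit times, patient entry "is defined as the latest of study start date, the date of diabetes diagnosis, and the date first evaluable for events". A patient becomes evaluable through BMI, HbA1c, blood pressure or prescription data, "since these records confirm that a patient was in Scotland at the time and can therefore be considered evaluable for events". No screening examination is needed. The same paragraph then adds: "Note that for the modelling purposes patient entry date will be further refined to be S2 day +1". Follow-up ends, among other reasons, at "or the date of the first event of interest".

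Under Event dates, "The date of the event will be taken as the date of screening on which referable retinopathy was detected".

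Two descriptive outputs depend on these definitions. Objective 1 asks for age-, sex- and type-specific "rates of first referable retinopathy in the screening programme and describe these by calendar year". The Initial tabulations say: "Show the number (%) and event rate of incident events during follow up", and then call for age-standardised rates. Neither section gives its own entry date. S1 and S2 are not defined. The only indication of their meaning is an example under Data formatting: "If a patient has had 5 screening episodes after entry (so s1 s2 then 5 after that".

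**The concern.** A first screening cannot show whether referable disease is new or has been there for years. Under the general entry rule, a patient with long-standing diabetes whose first examination after entry finds referable disease adds one event, set against only the time between entry and that examination. The SAP itself allows for patients with no earlier examination, because its one-step survival analysis includes a stratum with none. Nothing in the text removes first-screening detections from the rates or reports them separately.

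The rates are Objective 1's whole output, and the tabulations call the events incident. If they contain prevalent disease, they overstate or blur incidence, they describe a different risk set from the one modelled, and their course over calendar years partly reflects when patients were first screened.

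**Working it through.** The SAP states no rate, prevalence or event count on this point, so there is no figure to reproduce. The check has three steps.

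**1. What the text implies.** Entry needs no screening, the event is dated at the detecting screening, and exit is at the first event. A positive first screening after entry is therefore a first event under the general rule. Under S2 day +1 the same patient exits before entering and so drops out. The two entry dates give different event counts from the same data.

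**2. Pooled inflation.** All inputs are assumptions: incidence i = 0.01 to 0.02 a year, follow-up T = 5 years, share first screened after entry f = 0.2 to 0.5, prevalence at that screening p = 0.02 to 0.10.

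Ratio = (i × T + f × p) / (i × T)

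- Lowest: (0.10 + 0.2 × 0.02) / 0.10 = 1.04, or 4% inflation.
- Highest: (0.05 + 0.5 × 0.10) / 0.05 = 2.00, or 100%.
- At p = 0.05: from 0.2 × 0.05 / 0.10 = 10% to 0.5 × 0.05 / 0.05 = 50%.

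If all first screenings fall in the first year after entry, that year's ratio is (i + f × p) / i. It runs from (0.02 + 0.004) / 0.02 = 1.2 to (0.01 + 0.05) / 0.01 = 6.

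These formulas add the prevalent cases to a full five years of incidence and contain no calendar time. They say nothing about trend.

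**3. Calendar-year pattern.** This is a yearly cohort calculation (rate = events / person-years) with constant true incidence, annual screening and new diagnoses equal to 6% of the 2007 stock each year. Patients screened before 2007 are taken to be free of earlier referable disease. Incidence is set at 1% or 2.5%, borrowed from the example risk thresholds under Utility assessment; the SAP does not give these as incidences.

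Worked example for 2007 (1% incidence, first-screening prevalence 5% in the stock and 2% in new diagnoses, half the stock unscreened):

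- Events: 0.5 × 0.05 + 0.5 × (1 − e^−0.01) + 0.06 × 0.02 = 0.0250 + 0.0050 + 0.0012 = 0.0312.
- Person-years, with half a year lost per event: 0.4875 + 0.4975 + 0.0594 = 1.0444.
- Rate: 2.98 per 100 person-years, where the true rate is 1.0.

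| Incidence | Prevalence, stock / new | Stock unscreened before 2007 | 2007 | 2015 | Ratio |
|---|---|---|---|---|---|
| 1% | 5% / 2% | none | 1.06 | 1.04 | 1.01 |
| 1% | 5% / 2% | a quarter | 2.02 | 1.04 | 1.9 |
| 1% | 5% / 2% | half | 2.98 | 1.04 | 2.9 |
| 1% | 5% / 2% | all | 4.95 | 1.04 | 4.7 |
| 1% | 10% / 2% | all | 10.03 | 1.04 | 9.6 |
| 2.5% | 5% / 2% | all | 4.95 | 2.48 | 2.0 |
| 2.5% | 2% / 1% | all | 1.96 | 2.43 | 0.81 |

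In the last row, the yield of the first screening is below one year's incidence, so the early rate is diluted rather than inflated. With 1% incidence, 5% / 2% prevalence, the whole stock unscreened and first screenings spread over three years, the rates are 1.70, 1.98 and 2.24, then 1.05: a rise followed by a drop.

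When only events and person-time after a first screening free of referable disease are counted, the rate equals the true value (1.0 or 2.5) in both 2008 and 2015 in every scenario.

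**The case against.** The strongest reply is that the tabulations may already use the post-S2 data. The Data formatting example treats entry as coming after s1 and s2, Event dates flags events within person-time intervals, and the tabulations follow directly. On that reading no first-screening disease is counted. The reading is possible, because the SAP does not say where modelling purposes end. It is not stated, however, and the plain text confines the refinement to modelling.

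A second reply is that Objective 1 speaks of first referable disease in the programme, which could legitimately mean all first detections, that is, programme yield. A descriptive population wider than the modelled one is not in itself an error. That stands, but it conflicts with the word *incident* in the tabulations, and yield by calendar year should not then be read as a trend in incidence.

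Third, the size rests on assumptions. That also stands: the low end of 4% is small, and the SAP does not give the inputs that would narrow the range.

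Two stronger readings are tempting and are not supported:

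- A reader might infer that the rates will show a spurious fall over time. That requires the share of first screenings to change over the years. The SAP does not say when screening began or how many patients were screened before 2007. If the stock had already been screened, almost no trend results.
- A reader might take S2 day +1 to be a rule that patients must be clear of disease at entry. The SAP requires no clear result at S1 or S2. Patients positive at either drop out only because their exit would precede their entry.

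**Conclusion.** The point holds for the descriptive rates. As written, Objective 1 and the Initial tabulations start at an entry date that requires no prior screening, so disease present at a first screening is counted as incident. Under the stated assumptions the pooled rate is inflated by about 4% to 100%. If first-screening yield is lower than a year's incidence, the rate can instead be slightly too low. The calendar-year pattern can be distorted in either direction: with true incidence constant, the 2007/2015 ratio in the scenarios run lies between 0.81 and 9.6, and is about 1.0 when the 2007 stock had already been screened. Which of these applies cannot be told from the SAP. Prediction models that start at S2 day +1, and their validation, are not affected.

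**What to change.** In the entry-date section and the Initial tabulations:

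- Define S1 and S2, and state which entry date Objective 1 and the tabulations use.
- For those rates, start incidence person-time the day after the first screening free of referable disease, or use S2 day +1 as in the models. Exclude patients with earlier referable disease, including any recorded before 2007.
- Report referable disease found at the first screening separately, as prevalence. If programme yield is also wanted, tabulate all first detections under that name.
- Compute calendar-year rates on the same risk set, splitting person-time at 1 January.

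The cost is a few sentences, one extra table, some lost early person-time, and incidence rates that may be lower. No new data are needed.

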## **Endpoints**

The primary endpoint will be referable retinopathy

Secondary endpoints are referable maculopathy alone and referable retinopathy without maculopathy

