### Utility assessment

To be expanded: We will compare the estimated number of screenings required to maintain interval disease rate below a given threshold using the maximally predictive model from the above process with a much simpler decision algorithm such as i) the current annual screening for all programme and ii) a programme that would screen all type 1s annually and all types 2s biannually.

Since there are many ways in which policy formulations might utilise prediction risk. We will produce some examples; for instance we can show what the impact on number of screens per annum based on individualised screening intervals set by a series of thresholds of risk (e.g. 1% or 2.5% or 3%). We can also calculate the number of people who will potentially have a delay of >3 months in detection of referable disease and calculate the median 'delay' for each scenario (i.e. the interval between when they would have been screened based on current screening scheme and when they would be screened under the new scheme). The aim is that the models will be able to evaluate a wide range of potential screening policies to provide interactive feedback to policy makers.

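### Suspension from screening for eye disease, without an earlier referable grade, is neither an event nor an exit, so the observed rate of first referable retinopathy is understated by an unknown amount

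*SAP*

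**What the plan says.** **Exit.** Under Inclusion criteria, entry and exit times, a patient leaves at study end, death, the first event or the date last evaluable. Apart from death and study end, that last date rests on two things. One is "the date last observable for routine data or drug data (i.e. exit from the country"), extended by 183 days. The other is "Date of suspension from screening for non eye disease related reason". The clause that lets patients re-enter at a further screening refers to this second group. Suspension for an eye-related reason has no rule.

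**Entry.** Entry is the latest of study start, diagnosis and the first clinical or prescription record. A later start, the day after the second screening, applies to the modelling only.

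**Event.** Endpoints says "The primary endpoint will be referable retinopathy", without limiting it to disease found at screening. Event dates says "The date of the event will be taken as the date of screening on which referable retinopathy was detected" and names no other source. It adds: "We also have a censor date (which is the earliest of death/event/study end date/end of observability"). A zero flag in the last interval means censoring for a reason other than the event.

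**Rows.** Data formatting says "The data are split longitudinally from a patient's entry date to their exit or censor date". Its example, "If a patient has had 5 screening episodes after entry (so s1 s2 then 5 after that"), yields five rows.

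**Use.** Utility assessment compares policies by the "estimated number of screenings required to maintain interval disease rate below a given threshold".

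**The concern.** The suspension rule separates eye from non-eye reasons and then provides for only one of them. Where a suspension for eye disease follows a referable screening grade, the event rule has already ended follow-up and nothing is lost. The gap is the patient whose eye disease came to light by another route, or whose suspension is for a different eye condition. That patient is no longer screened, so no event can be recorded. HbA1c, blood pressure and prescription records carry on, so observability does not end either.

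Two things are at stake. The descriptive rates of Objective 1 would miss events and include time in which no event could be recorded. The absolute risks from the models, which are to be set against example thresholds of 1%, 2.5% and 3%, would be too low by about the same proportion. The 30% validation set is drawn from the same records under the same rules, so its calibration would not reveal the problem.

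**Working it through.** **The rules applied to one patient.** Take a patient with two non-referable screenings who is then suspended for eye disease found elsewhere.

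1. Event? No. No screening detected referable disease.
2. Exit through the suspension rule? No. The reason is eye-related.
3. Exit through observability? No. Routine and prescription records continue.
4. Exit at death or study end? Only when that date arrives, and then with flag 0.

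The hospital admissions linked under Data sources are not used to identify eye events, so they do not close the gap.

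**What enters the models.** Data formatting supports two readings. If rows run to the exit or censor date, the time after suspension counts as event-free. If there is one row per screening, as in the example, that time drops out. The event is uncounted on both readings.

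**Size.** The SAP gives no event rate, event count or share of disease found outside screening, so there is no figure to reproduce. Every input below is an assumption except the study window, 01/01/2007 to 01/06/2016 (9.42 years), and the hazards in the second check, which borrow the SAP's example thresholds.

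*Closed form.* Let f be the share of first referable disease found outside screening, r the true yearly rate and k the years of later event-free time per missed case. With D true events in P person-years, r = D/P. The observed rate is D(1 − f)/(P + D·f·k), so

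observed/true = (1 − f)/(1 + f·r·k).

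With r = 0.02 and k = 2:

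- f = 2%: 0.98/1.0008 = 0.979
- f = 5%: 0.95/1.002 = 0.948
- f = 10%: 0.90/1.004 = 0.896
- f = 20%: 0.80/1.008 = 0.794

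If the shortfall is uniform, a predicted 2.5% stands for 2.5/0.979 = 2.55%, 2.5/0.948 = 2.64%, 2.5/0.896 = 2.79% or 2.5/0.794 = 3.15%.

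*Simulation.* There were two million patients per scenario, with a constant hazard of 1%, 2.5% or 3% per year and annual screening. Entry was spread evenly over the first 7 of the 9.42 years, and nobody returned to screening after outside detection. The reference counts outside-detected disease when it is found. Ranges are across the three hazards.

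| f | A: event-free to exit | B: rows end at last screening | C: censored at outside detection |
|---|---|---|---|
| 2% | 0.976–0.977 | 0.978–0.979 | 0.978–0.979 |
| 5% | 0.941–0.943 | 0.945–0.947 | 0.945–0.946 |
| 10% | 0.883–0.890 | 0.893 | 0.892–0.893 |
| 20% | 0.771–0.782 | 0.788–0.789 | 0.786–0.787 |

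The largest gap between A and C is 0.787 − 0.771 = 0.016. The false event-free time therefore adds little; the shortfall is mainly f itself. B and C fall slightly below 1 − f because the reference counts outside-detected disease at once, while other disease waits for the next screening and some of it falls beyond the end of follow-up.

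**The case against.** **The size is assumed.** This stands. The SAP gives no share, and the calculation mostly returns the share that was put in. At 2% the ratio is 0.98, which would matter little.

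**Eye-disease suspension may always follow a referable grade.** That is a natural reading of why only non-eye reasons are listed, and if true it would leave nobody affected. The SAP does not say so, and eye disease is a wider category than referable retinopathy. A protocol not seen here may describe the pathway, but the rule as written does not depend on it.

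**The target may be screen-detected disease.** Objective 1 speaks of rates in the screening programme, and on that view disease found elsewhere is not a missed event. This is a good reason not to count suspensions as primary events: a suspension is not a graded result, it cannot be assigned to the maculopathy or non-maculopathy endpoint, and the SAP documents only an eye/non-eye split. It does not justify keeping patients at risk while they cannot be screened. Objective 2 is also worded more broadly, as time to first referable disease.

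**Such patients are eventually censored.** True: they leave at death, study end or loss of observability. The defect is that nothing happens at suspension. On the one-row-per-screening reading, the modelling data may already omit the later time.

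**Stronger readings.** A reader might infer that the missed cases are the highest-risk patients and that the strongest predictors are therefore weakened. The SAP says nothing about how these patients differ. A uniform loss of events in a log-linear Poisson model lowers the intercept and leaves the coefficients alone. A reader might also infer that the endpoint misses exactly the interval disease that Objective 4 is about. The SAP does not define interval disease, and Utility assessment is marked as still to be expanded.

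**Conclusion.** The concern holds as a gap with a known direction and an unknown size. Followed literally, the exit and event rules leave a patient suspended for eye disease without an earlier referable grade with no event and no exit at suspension. For Objective 1 they also keep people already suspended at entry in the denominator; the later modelling entry date does not apply there, and this part has not been quantified.

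The observed rate is understated on either reading of the row structure. Under the stated assumptions it is about 0.98, 0.95, 0.89 or 0.79 of the true rate for shares of 2%, 5%, 10% or 20%, and up to about 0.02 lower if event-free time also enters. These ratios assume that outside-detected disease belongs to the target and that those patients do not return to screening; disease found at a later return would be counted late, not lost. The change should be made because a stated rule causes the bias and the repair is small, not because a large effect has been shown.

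**What to change.** 1. In Inclusion criteria, entry and exit times, exclude from the at-risk set anyone suspended for eye disease at entry until a later non-referable screening.
2. In the same section, end evaluability at the last screening before any eye-disease suspension that has no earlier referable grade. Align Event dates and Data formatting with this, and state whether rows continue after the last screening.
3. Add a sensitivity analysis that counts these suspensions as events, interval-censored between the last screening and the suspension date. Limit it to diabetic eye disease if the recorded reason allows. Report how many there are, by diabetes type.

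Step 3 is needed because censoring alone does not restore the uncounted events: columns B and C of the table stay close to 1 − f.

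The cost is a few sentences and a short data step. The existing rule already relies on the suspension reason being recorded at the eye/non-eye level; whether diabetic and other eye disease can be separated has to be checked. The downside is slightly less person-time, and inexact event dates in the sensitivity analysis.
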